### Inclusion and exclusion criteria

Participants who meet the following criteria will be eligible:Spend the majority of their day sitting (> 50%). This will initially be self-reported and be used as screening criteria prior to the consent and baseline measurement visit. This will subsequently be confirmed using the objective data collected via the activPAL device (see measures section).Work for the council at least 60% full time equivalent.Work in the same office at least 3 days per week.Be willing and able to give informed consent to take part in the study.Able to walk without the use of an assistive device or requiring assistance from another person.

The participant may not enter the study if any of the following apply:They are currently pregnant.Currently using a height-adjustable workstation at their primary work location.Unable to communicate in English.Unable to provide written informed consent.

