#### Demographic, medical history and medication

During their baseline visit, participants will be asked their age and date of birth, ethnicity, education level, current job role and pay grade, working site, working hours, length of time in post, number of people in their office and department, postcode and household composition. At each follow up visit, participants will be asked if there has been any change in these aspects.

Details of any history of disease or injuries that may indicate an inability to participate in the study will be measured. If needed, results will be reviewed to define eligibility. Medication will also be recorded.

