#### Process evaluation

The process evaluation methods will be a mix of questionnaires, interviews, focus groups and direct observation. The process evaluation will be used to understand: the participants’ experiences of the intervention and its different components; any discrepancies between expected and observed outcomes; the influence of intervention components and context on the observed outcomes; sustainability; the extent of any contamination between intervention and control; and, any unexpected events arising from participation. Completion of education and attendance at coaching sessions will be recorded. Self-report questionnaires provided to study participants will evaluate their opinions of the various intervention components (e.g. education, coaching, self-monitoring, workstation). Interviews and focus groups with study participants (sub-sample) will further examine engagement in the various components of the intervention, along with any barriers or facilitators to participating in the various components. Focus groups with workplace champions will further examine the intervention implementation and the champions’ experiences of delivery. All interviews and focus groups will be audio-recorded and transcribed verbatim.

Throughout the intervention we will monitor the fidelity of the intervention implementation using the Normalisation Process Theory framework [66] in line with guidance from the National Institutes of Health Behaviour Change Consortium and the DESMOND collaborative. Observations or recordings (via voice recorder) of sessions (e.g., coaching) will take place in both intervention arms to assess whether the content was delivered as expected and receipt of the intervention by attendees. During the observations a case report form will also be completed. The case report form will combine an ‘adherence measure’ to capture delivery (mode of delivery (dose)/duration/content) and use of resources (materials/activities). The structured observation tool will assess facilitator delivery of prescribed behaviours and behaviour change techniques. The case report form will also contain specific objective ‘receipt’ measures and will likely include examples related to how well the participants understand the content and engage in the session.

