#### Cost effectiveness

The economic evaluation will consist of two analyses. i) a cost-consequence analysis based on the observed results within the trial period and ii) a cost-effectiveness analysis where differences between groups in the trial will be extrapolated to the longer term where appropriate.

For both analyses, costs in both arms will be estimated from a National Health Service (NHS) and Personal Social Services (PSS) perspective (consistent with that used by the National Institute for Health and Care Excellence (NICE)) as well as a wider public sector perspective. In each analysis, the cost of the SMART Work & Life groups will include an estimate of the cost of the intervention, with and without the height adjustable desk. The cost of the intervention consists of the cost of equipment (such as desks) and the cost of training and delivery of intervention. We will estimate the cost of the equipment from manufacturer’s estimates of costs. We will also estimate the cost of training and delivery of intervention by the workplace champions.

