##### Within-trial analysis

Within the period of the trial, we will collect resource use estimates from participant questionnaires. These questionnaires will record health related resource use as well as absence from employment. The health related resource use will be based on a variant of the Client Service Receipt Inventory and will include services that this population are likely to utilise such as GPs and Practice nurse appointments, occupational health visitors and other professionals that are deemed appropriate. Costs of resources will be calculated by applying published national unit cost estimates (e.g. NHS reference costs or Personal Social Services Research Unit costs of health and social care), where available, to estimates of relevant resource use.

A range of outcomes will be assessed in the trial including health related quality of life, measured using the EQ5D-5 L The within trial analysis will present incremental results for the primary and secondary outcomes (including EQ5D) in both intervention and control arms and will be compared with the incremental costs measured above. We will also present the results in terms of the differences in time absent from work between the groups. As there is some controversy over inclusion of productivity losses in the assessment of cost-effectiveness, the within trial analysis will be presented both with and without estimates of the cost of sickness absenteeism. This will allow decision makers to assess the importance of inclusion of absenteeism costs when deciding whether to implement the intervention.

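### The intervention cost leaves out employees' working time in the education and coaching sessions, so the wider public sector cost against control is understated to the extent that the sessions fall in paid time

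*Protocol article*

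**What the plan says.** The Cost effectiveness section takes two perspectives for both the within-trial and the longer-term analysis: NHS and Personal Social Services, "as well as a wider public sector perspective". It carries the intervention cost into both: "In each analysis, the cost of the SMART Work & Life groups will include an estimate of the cost of the intervention". That cost is then defined: "The cost of the intervention consists of the cost of equipment (such as desks) and the cost of training and delivery of intervention". Equipment comes from manufacturers' figures. On the other component the article says: "We will also estimate the cost of training and delivery of intervention by the workplace champions".

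Under Main intervention components, the individual and group strategies give participants one online education session and four group coaching sessions led by champions. The control arm carries on with usual practice.

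Under Within-trial analysis, the results "will be presented both with and without estimates of the cost of sickness absenteeism". Longer term analysis likewise includes and excludes productivity losses.

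Two items collected for other purposes bear on the remedy. Process evaluation, under Measurements, says: "Completion of education and attendance at coaching sessions will be recorded". The baseline visit collects "current job role and pay grade".

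**The concern.** The definition of intervention cost reads as a complete list. It counts the time of the person who runs a coaching session but not the time of the colleagues who sit in it. Participants are public sector staff (the eligibility criterion is "Work for the council at least 60% full time equivalent"), so any paid time they spend falls on the council, a payer inside the wider public sector perspective that the protocol has chosen. Controls have no such sessions, so the omitted cost is wholly incremental against control.

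In the versions with absenteeism or productivity losses there is a further imbalance. An hour of work regained through less sickness counts in favour of the intervention, while an hour of work given to the intervention counts for nothing. These results are meant to help decision makers judge whether to adopt the programme, and for an employer the staff time it takes up is a relevant cost.

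**Working it through.** The article gives no intervention cost, session length or wage, so there is no stated figure to reproduce. The check has two parts: which costs are counted, and an illustration of size.

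**Which costs are counted**

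| Resource | Source in the article | Valued in the economic sections? |
|---|---|---|
| Equipment, including desks | Cost effectiveness | Yes |
| Champions' training and delivery | Cost effectiveness | Yes |
| Participants' time in 1 education session | Main intervention components | Not named |
| Participants' time in 4 coaching sessions | Main intervention components | Not named |
| Work time lost to sickness | Within-trial analysis | With and without |
| Productivity losses | Longer term analysis | Included and excluded |

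**Illustrative size**

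From the documents:
- Sessions per participant: 1 + 4 = 5.
- Recruited cluster size: 20, and 14 before inflation (Sample size).
- Participants in the two intervention arms: 2 arms × 11 clusters × 20 = 440.

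Assumed, because the documents give neither:
- 15 to 60 minutes per session. The article describes the coaching as brief, so the upper end is generous.
- An employment cost of GBP 15 to 25 per hour.
- All five sessions attended, all in paid time.

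Omitted hours per participant = 5 × session length:
- low: 5 × 0.25 h = 1.25 h
- high: 5 × 1 h = 5 h

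Omitted cost per participant = hours × hourly cost:
- low: 1.25 × 15 = GBP 18.75
- high: 5 × 25 = GBP 125

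Per cluster of 20: 20 × 18.75 = GBP 375 to 20 × 125 = GBP 2,500.

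Over both intervention arms: 440 × 18.75 = GBP 8,250 to 440 × 125 = GBP 55,000.

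With an assumed working day of 7.4 h, the omitted time is 1.25/7.4 = 0.17 to 5/7.4 = 0.68 of a day per participant. In the productivity-inclusive versions, that is the amount of avoided absence per participant that would only offset the time spent in the sessions.

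One ratio needs neither a wage nor a duration. If one champion coaches a whole cluster of 14 to 20 in one meeting, 14 to 20 attendee hours go uncounted for each champion hour counted in that meeting. This compares time within coaching sessions only. It says nothing about the share of the total intervention cost, which also contains desks, champion training and the champions' other tasks.

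**Where it matters**

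- Each intervention arm against control, wider public sector: understated by hours attended × hourly cost.
- The same comparison with absenteeism or productivity losses included: the same shortfall, together with a credit for time saved.
- NHS/PSS: council employees' time would not ordinarily be a cost here, so these results are largely unaffected.
- Arm 1 against arm 2: both receive the same components except the workstation (Intervention arms 1 and 2), so the omission largely cancels.

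**The case against.** A reader might infer that cost-effectiveness as a whole is biased in favour of the intervention. The documents do not support that. Absence is not simply costed on one side: the within-trial results appear with and without it, and the longer-term results with and without productivity losses, so the imbalance with time saved arises only in the inclusive versions. One of the two perspectives and one of the trial's comparisons are largely untouched.

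A reader might also take it that every participant completes all sessions in paid time at the workplace. The article does not say that the sessions are in paid time, and gives no durations. That completion and attendance are recorded leaves room for partial uptake. If the education is done at home or the coaching in unpaid breaks, less is omitted, possibly nothing. No total intervention cost is available, so it cannot be shown that a conclusion would change. All of this stands, and it limits scope and size.

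Two arguments go further. Training and delivery might be read to cover the time of those being trained, and a condensed article may leave itemised staff costing to a fuller health economics plan. Neither removes the point. The article states what the cost consists of and then attaches training and delivery to the champions. An analyst following it as written would leave participants' time out.

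**Conclusion.** The point holds in a limited form. The stated definition omits participants' working time in the education and coaching sessions. To the extent that the sessions fall in paid time, the incremental cost of each intervention arm against control is understated in the wider public sector analysis, and the versions that include absenteeism or productivity losses credit time saved without debiting time used. Reporting with and without absenteeism does not cure this, because participants' time is absent from both versions.

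The direction against control is clear and the amount is not. The range of roughly GBP 19 to 125 per participant rests wholly on assumed session lengths, hourly costs, full attendance and paid time. With short sessions or partial attendance it would lie at or below the lower end.

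**What to change.** In the wider public sector analysis, and wherever productivity losses are included, add to the intervention cost:

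participant time cost = recorded attendance × session duration × hourly cost for the pay grade.

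Count only sessions held in working time, and state how that was established. Report the results with and without this item, next to the existing versions with and without absenteeism.

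Most inputs are already planned: education completion and coaching attendance are recorded, duration is captured for observed sessions, and pay grade is collected at baseline. For the online education session, a stated nominal length may be needed if its duration is not captured.

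The cost is some additional analysis, with no change to the design or to the primary analysis. The downside is a somewhat less favourable cost per outcome for both intervention arms against control.

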##### Within-trial analysis

Within the period of the trial, we will collect resource use estimates from participant questionnaires. These questionnaires will record health related resource use as well as absence from employment. The health related resource use will be based on a variant of the Client Service Receipt Inventory and will include services that this population are likely to utilise such as GPs and Practice nurse appointments, occupational health visitors and other professionals that are deemed appropriate. Costs of resources will be calculated by applying published national unit cost estimates (e.g. NHS reference costs or Personal Social Services Research Unit costs of health and social care), where available, to estimates of relevant resource use.

A range of outcomes will be assessed in the trial including health related quality of life, measured using the EQ5D-5 L The within trial analysis will present incremental results for the primary and secondary outcomes (including EQ5D) in both intervention and control arms and will be compared with the incremental costs measured above. We will also present the results in terms of the differences in time absent from work between the groups. As there is some controversy over inclusion of productivity losses in the assessment of cost-effectiveness, the within trial analysis will be presented both with and without estimates of the cost of sickness absenteeism. This will allow decision makers to assess the importance of inclusion of absenteeism costs when deciding whether to implement the intervention.

##### Longer term analysis

While there may be short term health benefits from reducing levels of sitting time, the longer term effects on mortality on office workers is likely to be more important. We will therefore use existing evidence that links short-term trial endpoints and longer term outcomes. While some existing evidence used covariates to adjust for confounding factors, it is not possible to assess unmeasured confounders. Therefore, we will use existing evidence to extrapolate costs and effects to a more appropriate time horizon; however, as recommended by Taylor and Elston [67] we will explain how the surrogate-final outcomes relationship is quantified and explore the uncertainty around the use of the surrogate outcome (in this case sitting time) through sensitivity analysis.

If appropriate an Incremental Cost-effectiveness Ratio for the extrapolated period will be reported using the Quality Adjusted Life Year (QALY). As with the within-trial analysis, we will conduct analyses where productivity losses are included/excluded to assess the impact on decision making. Costs and effects will be discounted at the prevailing recommended rate (currently 1.5% per annum on both costs and effects), but will be the subject of sensitivity analysis to reflect the ongoing uncertainty around appropriate discount rates for public health interventions. We will conduct probabilistic sensitivity analyses to allow a characterisation of the uncertainty around the adoption decision which we will depict using cost-effectiveness acceptability curves. Sensitivity analyses will be performed to determine the robustness of the results to altering certain assumptions such as the discount rate, inclusion/exclusion of productivity losses and the robustness of the relationship between sitting time and mortality.

### Data handling

All data collected will be kept strictly confidential and in accordance with all relevant legislation. The participants will be identified on documentation by a unique ID number, not by name (apart from on the consent form and enrolment log). All research data will be kept in a secure location within University of Leicester, University of Salford or the University Hospitals of Leicester, accessible only by named members of the research team during the active phase of the study and until the data have been analysed. It will then be archived in line with University of Leicester policy. The Leicester Clinical Trials Unit will be providing a Good Clinical Practice compliant database solution using a Clinical Data Management System called InferMed Macro. This is a secure and validated database solution with quality control mechanisms to ensure that the data collected are complete and accurate.

## Discussion

Office workers exhibit high levels of sitting both inside and outside of work [7, 8], with accumulating evidence demonstrating the detrimental impacts of high levels of sedentary behaviour on health [3–6] interventions in this population are needed. Although previous workplace interventions have shown promise in reducing sitting time [22, 23] study designs have been of low quality [22, 23], with only a handful of fully powered cluster randomised controlled trials being conducted [24, 25].

Strengths of this study include the robust randomised controlled trial design, with randomisation at the cluster level to reduce contamination, the large fully powered sample, the inclusion of short, medium and longer term follow up measures, the extensive quantitative and qualitative process evaluation, the rigorous economic evaluation and the use of an objective measure of physical activity as the primary outcome. Furthermore, this study is unique, in that it will be delivered at two levels i.e., with and without the provision of a height-adjustable workstation. These study aspects will all contribute to building the evidence base around the effectiveness of interventions to reduce sitting time and inform policy guidelines for population and workplace health and wellbeing.

## Abbreviations

BCW: Behaviour change wheel
BMI: Body mass index
BP: Blood pressure
COM-B: Capability, opportunity, motivation-behaviour
CONSORT: Consolidation Standards of Reporting Trials
DMC: Data monitoring committee
GP: General practitioner
HDL: High-density lipoprotein
ICC: Intraclass correlation coefficient
LDL: Low-density lipoprotein
MVPA: Moderate-to-vigorous physical activity
NHS: National Health Service
NICE: National Institute for Health and Care Excellence
PSS: Personal social services
QALY: Quality adjusted life year
RCT: Randomised controlled trial
WHO-5: World Health Organisation-Five Well-Being Index
